The internalization of stigma, i.e., self-stigma, is thought to be one of the main causes of the reduced social inclusion of people with SMI [9–11]. Self-stigma is defined as the process by which an individual internalizes negative messages about their own social group and applies them to themselves [12]. This phenomenon, which is strongly associated with negative emotions (i.e., shame) [13], self-critical thoughts, and a significant fear of public stigma—that is, stigmatizing attitudes and behaviors from others [3]—prevents individuals from fulfilling and pursuing their life goals [14]. In particular, self-stigma is involved in diminished coping skills that lead to social avoidance and difficulties in adhering to care [7]. Considered as the affective component of self-stigma [13], shame is highly associated with negative self-evaluation and self-criticism, greater severity of clinical presentations, and impeding treatment [15–17]. In addition to increasing the risk of psychopathology, shame can thus be a hindrance to the effectiveness of treatments as it influences the expression of symptoms and the patient’s ability to disclose painful information and to seek help, and it can promote several types of avoidance, such as dissociation and therapy drop-out [16].

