#### Objectives {7}

The primary objective of our study is to evaluate the efficacy of a 12-week CFT group in decreasing self-stigma associated with severe psychiatric disorders and ASD by comparing its immediate effects to the effects of the Ending Self-Stigma (ESS) psychoeducation program [29] and to TAU.

The secondary objectives of our study are as follows:1. To evaluate the maintenance of effects on self-stigma scores in the three groups of treatment (CFT, ESS, and TAU) at 6-month follow-up (V2)2. To assess the effects of treatment (CFT, ESS, and TAU) at baseline (V0), post-treatment (V1), and at 6 months follow-up (V2) on target psychological dimensions (shame, self-compassion, emotional regulation, automatic avoidance tendencies toward mental illness)3. To assess the effects of treatment (CFT, ESS, and TAU) at baseline (V0), post-treatment (V1), and at 6 months follow-up (V2), on social functioning and psychiatric measures (psychiatric symptoms, depression, anxiety and stress, social functioning, access to care, recovery, functional remission)4. To assess the psychological factors mediating (shame, self-compassion, and emotional dysregulation) the efficacy of CFT on the self-stigma measure (V1)5. To evaluate the acceptability of the active interventions (CFT and ESS): pretreatment (V0) via a treatment credibility measure, during treatment via attrition rate, session attendance and group cohesion, and post-treatment (V1) via patient satisfaction and treatment side effects In addition, in the coordinating center, qualitative interviews will assess the acceptability of the active interventions.

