### Outcomes {12}

#### Primary outcomes

The decrease in scores on the Internalized Stigma of Mental Illness Scale (ISMI) [31] will be our primary outcome. The ISMI scale has good psychometric qualities in its various language versions [20]. This measure is a 29-item self-report questionnaire with five subscales: (1) alienation, (2) endorsement of perceived stereotypes, (3) discrimination, (4) social withdrawal, and (5) resistance to stigma. The participant must select their response on a 4-point Likert scale ranging from strongly disagree (1) to strongly agree (4).

The ISMI scale will be administered before therapy (V0), at the end of therapy (V1), and 6 months after the end of therapy (V2). If CFT is efficacious in reducing self-stigma, ISMI scores will decrease significantly between V0 and V1, and this decrease will be greater for CFT than for psychoeducation (ESS) and TAU.

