### Secondary outcomes

Assessment of the maintenance of self-stigma scores:• To evaluate the maintenance of effects on *self-stigma* in the three groups of treatment (CFT, psychoeducation, and TAU) at 6-month follow-up (V2) the Internalized Stigma of Mental Illness Scale (ISMI) [31] will be applied.

Assessment of the effects of treatment (CFT, psychoeducation, and TAU) at baseline (V0), post-treatment (V1), and at 6 months follow-up (V2) on target psychological dimensions and assessment of the psychological factors mediating the efficacy of CFT on the self-stigma measure:The Internalized and Externalized Shame Scale (EIS) [53] will be used to measure shame. It consists of 9 items ranging from 1 (not at all) to 4 (a lot).The Phenomenological Body Shame Scale – Revised (PBSS-R) [54] will also be used to measure body-related shame. Each of the 8 items is scored on a scale ranging from 1 (not at all) to 5 (extremely).The Self-Compassion Scale (SCS) [55] will be applied to measure self-compassion. The 26 items are scored on a scale ranging from 1 (almost never) to 5 (almost always).The Difficulties in Emotional Regulation Scale – 16 items version (DERS-16) [56] will be used to measure emotional regulation competencies. Each item is scored on a scale ranging from 1 (almost never) to 5 (almost always).The automatic avoidance tendencies toward mental disorders (VAAST) [57, 58] assesses the participants’ automatic avoidance tendencies toward mental disorders. The VAAST simulates the approach and avoidance movements of the whole self by manipulating the visual information provided to the participants. A stimulus first appears in the center of the screen in a simulated street background. Participants have to press the “move toward” or the “move away” key as a function of the stimulus category and the instructions. This complementary measure allows to circumvent some biases (such as social pressures) in the responses to the self-report scales.

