
The mechanisms underlying the relationship between the intervention and the primary endpoint will be identified by carrying out an estimation of the causal mediation effect using the Baron and Kenny procedure though the quasi-Bayesian approximation. This allows for obtaining total, direct, indirect effects and the percentage of mediation. The potential mediators that will be tested include self-compassion, shame, and emotional dysregulation.

The statistical analyses will be run with the following software: R (with all the relevant packages), OpenBUGS, and JAGS, in their most up-to-date version at the time of analysis.

There is no significance level in Bayesian statistics. An effect will then be considered significant if its probability to exceed a prespecified threshold value, given the data, is strictly larger than 0.975 or strictly lower than 0.025. Credibility intervals will be provided at 95%.

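### The mediators and ISMI are both read at V1, so the planned "causal" mediation model cannot tell shame lowering self-stigma from the reverse

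*Protocol article*

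**What the plan says.** Protocol article, Objectives {7}, fourth secondary objective: "To assess the psychological factors mediating (shame, self-compassion, and emotional dysregulation) the efficacy of CFT on the self-stigma measure (V1"; the bracket names the post-treatment visit.

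Statistical methods {20a} states the ambition: "The mechanisms underlying the relationship between the intervention and the primary endpoint will be identified". The means is "an estimation of the causal mediation effect using the Baron and Kenny procedure though the quasi-Bayesian approximation", which is to yield total, direct and indirect effects and a percentage of mediation. It adds: "The potential mediators that will be tested include self-compassion, shame, and emotional dysregulation".

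Timing comes from the outcomes section {12}. The mediator scales serve to assess effects "at baseline (V0), post-treatment (V1), and at 6 months follow-up (V2) on target psychological dimensions and assessment of the psychological factors mediating the efficacy". ISMI has the same three visits. The section on follow-up visit V1 places ISMI within the self-report questionnaires given at that visit. The only questionnaire scheduled during treatment is the group cohesion measure (sessions 1, 6 and 12), which is not a mediator.

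On the constructs, Background {6a} describes shame thus: "Considered as the affective component of self-stigma". The Discussion states the directional hypothesis that change in shame mediates the effect of the intervention on self-stigma.

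**The concern.** A causal reading of an indirect effect needs the mediator to move before the outcome. Here the text fixes the outcome at V1 and schedules no mediator reading between the start of therapy and V1. A fall in shame that causes a fall in ISMI, and a fall in ISMI that causes a fall in shame, leave the same kind of V1 correlation within arms. The model credits both to shame.

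The risk is not remote, because the protocol itself treats shame as part of self-stigma. Mediation by shame is also the stated reason why CFT should do better than ESS. A reported percentage of mediation under a causal label would be read as confirming that theory.

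**Working it through.** **Inputs from the protocol.** Visits V0, V1 and V2 for mediators and ISMI ({12}); mediated outcome at V1 ({7}); 84 evaluable per arm ({14}); an effect counts as significant if its posterior probability is above 0.975 or below 0.025 ({20a}). The protocol gives no figure for the mediation analysis, so there is none to reproduce.

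**Assumptions, not in the protocol.** Linear models, two arms, path sizes as below, all models adjusted for V0 mediator and V0 ISMI. A simulated result counts as significant when the quasi-Bayesian 95% interval excludes zero.

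**Step 1: which mediator value is available?** V0 precedes therapy and V2 follows the outcome, so V1 remains. A V0-to-V1 change score uses the same V1 reading and does not help.

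**Step 2: size of the artefact.** Suppose treatment lowers ISMI, ISMI drives shame, and shame has no effect on ISMI. Given the V0 values, with T the arm:

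- S1 = −c·T + eS
- M1 = r·S1 + eM

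The fitted paths are a = −c·r and b = r·σS² / (r²σS² + σM²). The apparent share is ab/(−c) = r²σS² / (r²σS² + σM²), which is r²/(1 + r²) when the residual SDs are equal. The truth is 0.

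| Reverse path r | r²/(1 + r²) | Simulated, 3,000 trials |
|---|---|---|
| 0 | 0% | – |
| 0.3 | 0.09/1.09 = 8.3% | 8.1% |
| 0.5 | 0.25/1.25 = 20.0% | 19.9% |
| 0.7 | 0.49/1.49 = 32.9% | 32.7% |

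**Step 3: how often would mediation be declared?** Take r = 0.4, c = 0.5 baseline SD and residual SDs of 0.7. The share is 0.16/1.16 = 13.8%, so the spurious indirect effect is 0.138 × 0.5 = 0.069 SD (simulated: 0.068). In 600 simulated trials it was significant in 41%, or 26% if all scales have reliability 0.8.

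**Step 4: does moving the outcome to V2 help?** Let V2 ISMI = 0.6 × V1 ISMI + noise. If V1 ISMI is left out, the indirect and total effects both shrink by 0.6, so the share is unchanged. The spurious effect is 0.6 × 0.069 = 0.041 SD.

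| Model, no true mediation | Spurious effect, reliability 1.0 | Significant, reliability 1.0 | Significant, reliability 0.8 |
|---|---|---|---|
| V1 mediator to V1 ISMI (planned) | 0.07 SD | 41% | 26% |
| V1 mediator to V2 ISMI, V1 ISMI omitted | 0.04 SD | 30% | 15% |
| V1 mediator to V2 ISMI, V1 ISMI adjusted | 0.00 SD | 2% | 3% |

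At reliability 0.8 the adjusted model keeps a bias of about 0.01 SD. It is still there at 5,000 per arm, so it comes from measurement error and not from chance. When shame truly does act on later ISMI (assumed lagged path 0.25), the adjusted model finds it in 92% of trials, or 81% at reliability 0.8.

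**Step 5: a shared cause instead of a reverse path.** Let treatment lower shame by 0.5, let shame have no effect on ISMI, and let an unmeasured factor with SD 0.4 move both at V1. Then b = 0.16/(0.49 + 0.16) = 0.246, and the spurious indirect effect is 0.5 × 0.246 = 0.12 SD.

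**The case against.** **Mediator timing is not stated.** Section {20a} gives no visit for the mediators, and the V1 in objective 4 attaches to the self-stigma measure. That is correct; V1 mediators are an inference. No other reading gives a post-treatment mediator no later than the outcome, so the inference stands.

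**This is analysis-plan detail.** Covariates and a confounding sensitivity analysis are commonly left to the analysis plan, and their absence from an article is no fault. The point rests instead on what the text fixes: outcome visit, measurement schedule, causal label and the promise to identify mechanisms.

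**Stronger readings that the documents do not support.**

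- A reader might infer that a positive percentage of mediation is to be expected even if shame plays no causal role. It needs a reverse path or a shared cause. Shame's overlap with self-stigma makes one plausible, but the protocol gives no figure for either.
- A reader might blame the Baron and Kenny procedure. That label sits loosely beside the quasi-Bayesian approximation, but the fault is the shared visit, and the quasi-Bayesian estimator has it too.
- A reader might infer that the percentage is unstable because the total effect is only 0.10. That is CFT against ESS at V1 (2.20 − 2.10, {14}). CFT against TAU is 2.43 − 2.10 = 0.33, and {20a} does not say which contrast is mediated.
- A reader might infer that V1 mediators and V2 ISMI settle the direction. Step 4 shows that they do not unless V1 ISMI is in the model. Even then the overlap between shame and self-stigma remains.

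**The lag changes the question.** Objective 4 concerns the V1 effect, while the adjusted lagged model concerns further change to 6 months. This stands, and is why the lagged model should be added and not substituted.

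**Conclusion.** The concern holds in limited form. As written, the mediation analysis can attribute to shame an effect that it does not have, so it does not support the causal wording. With 84 per arm, the spurious share is about 8% to 33% of the total effect for reverse paths of 0.3 to 0.7. In the one case simulated for error rates, mediation is falsely declared in 26% to 41% of trials. These sizes rest on assumed paths, linear models and equal residual SDs. That same-visit data leave the direction open does not depend on those values.

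The point concerns a secondary objective and leaves the primary efficacy comparison untouched. What is at risk is the claim about mechanism.

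**What to change.** 1. Keep the V1 mediator to V1 ISMI model for objective 4, report it as associational, and replace the statement that mechanisms will be identified with wording to match.
2. Add to the quasi-Bayesian estimate a sensitivity analysis for unmeasured mediator-outcome confounding.
3. Add a lagged model of V1 mediator to V2 ISMI, adjusted for V1 ISMI, V0 ISMI and the V0 mediator. The version without V1 ISMI should not be the main one.
4. Fit the reverse lag, V1 ISMI to V2 mediator, for comparison.

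**Cost.** Analysis wording and some extra models; every measurement is already scheduled. The lagged model describes change from V1 to 6 months and not the V1 effect, loses participants who drop out before V2, and still assumes no unmeasured confounding and limited measurement error. It should be reported as supporting evidence on direction, not as proof of mechanism.

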## Statistical methods

### Statistical methods for primary and secondary outcomes {20a}

The statistical analysis will have descriptive and inferential. The analyses will be carried out according to Bayesian methods.

The descriptive statistical analysis of the categorical variables will be performed by giving the frequencies, the cumulative frequencies, the proportions, and the cumulative proportions of each value. Whenever useful, cross-tabulations will be given with frequencies, proportions by row, proportions by column, and proportions of the total for each box in the table. For each continuous variable, the location parameters (mean, median, minimum, maximum, first and third quartiles) and the dispersion parameters (variance, standard deviation, range, interquartile range) will be given. The continuous variables will be described with histograms (with different bin width and with kernel density estimation). The normality of the distributions will be tested using a normality test, such as the Shapiro-Wilk test, and will be assessed graphically using a normal quantile plot.

To fulfill the primary objective, a generalized Bayesian linear regression model will be performed in order to estimate the effect of the treatment considering the center and the subject as a random effect. According to the distribution of the primary endpoint, i.e., the ISMI, the linear regression will be Gaussian, beta, or gamma.

To fulfill the secondary objectives, a generalized Bayesian linear regressions model will be performed: binary variables will be analyzed with a Bayesian logistic regression, score variables will be analyzed with a Bayesian beta regression, count variables will be analyzed with a Bayesian Poisson regression, and continuous variables will be analyzed with a Bayesian linear regression.

Priors will be firstly weakly informative and secondly more informative in a sensitivity analysis.

For each analysis, the posterior distribution of the parameter of interest (rate, proportion, mean, odds-ratio, regression coefficient, etc.) will be estimated using Markov chain Monte Carlo (MCMC) draws. The default number of iterations is 100,000 with a burn-in of 10,000 and a thinning of 2 on each of 3 chains. Algorithm convergence will be assessed graphically and with the Gelman-Brooks-Rubin (GBR) test. Autocorrelation will be assessed graphically, and if required, the number of iterations and thinning will be increased to reduce as much as possible the autocorrelation.

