Indeed, if our 12-session group program produces a significant decrease in self-stigma and shame scores and improves participants’ social inclusion in a long-term perspective, it could become an empirically assessed viable option specifically suited to the needs of people presenting with SMI or ASD, whose quality of life is diminished due to high self-stigma. Moreover, in terms of format and content, this 12-session-manualized-group CFT has many advantages. Indeed, by targeting key transdiagnostic psychological processes—i.e., self-stigma and shame—it can increase the feasibility and dissemination of the intervention to a high number of clinical contexts (e.g., community health centers, different clinical populations).

Our study protocol presents some limitations. First, the distribution of diagnostic categories might present some inevitable variability across different hospital centers involved. However, our purpose is to propose a transdiagnostic intervention. Relatedly, facilitators’ backgrounds will vary depending on the centers, with possibly different training backgrounds and clinical experiences. To account for this limit, all group facilitators will be trained by the coordinating center clinical team during a 3-day-training specific to each intervention. Second, though concomitant psychotropic medications as well as the use of adjunctive therapeutic means (e.g., self-help or counseling) will be controlled in our study, participants will not be instructed to avoid making use of them. While this might be a potential confound in the current study design, the restriction of therapeutic options would also pose an ethical concern, reduce referrals to the study and also be a threat to external validity. Therefore, by monitoring therapeutic (i.e., medication or counseling) use throughout the trial, the current study seeks to balance the internal and external validity and improve the feasibility of the study while efficiently addressing its hypotheses.

If our innovative group CFT program can effectively reduce self-stigma and shame, it may facilitate the social inclusion of a large number of people with severe mental illness and/or ASD and significantly improve their quality of life and their physical and mental health by reducing barriers to access care.

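### One unadjusted posterior rule labels any effect significant, and nothing marks the many secondary results as supportive or exploratory

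*Protocol article*

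**What the plan says.** The relevant rule is in the protocol article under Statistical methods for primary and secondary outcomes {20a}. After stating that "There is no significance level in Bayesian statistics", it sets a fixed cut-off: "An effect will then be considered significant if its probability to exceed a prespecified threshold value, given the data, is strictly larger than 0.975". The mirror-image cut-off at the other end is 0.025, and 95% intervals accompany the estimates. The rule is written for any effect and has no exception. The threshold value itself is not given.

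The same section gives the secondary objectives the same kind of analysis: "To fulfill the secondary objectives, a generalized Bayesian linear regressions model will be performed". The model family follows the type of variable. No separate decision rule is given for these outcomes, and no model links them. On priors it says: "Priors will be firstly weakly informative and secondly more informative in a sensitivity analysis".

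Outcomes {12} separates the two levels clearly. The fall in ISMI "will be our primary outcome", and everything else is listed as secondary:

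- five instruments for psychological dimensions (EIS, PBSS-R, SCS, DERS-16, VAAST);
- six for functioning and symptoms (BPRS, EDAS-21, SFQ, BACES, RAS, Mini-FROGS);
- ISMI at V2;
- the acceptability measures.

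Objectives {7} adds three mediators. Nothing ranks the items within this secondary set or describes them as supportive or exploratory.

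**The concern.** Taken at its word, the rule lets a result on any secondary scale, at either visit and for either contrast, be reported as significant in the same terms as the primary result. Saying that Bayesian analysis has no significance level does not remove the issue, because the next sentence declares significance at a fixed posterior cut-off. With priors that hardly shrink the estimates, that cut-off gives a false declaration about once in 20 tests when there is no true difference. The plan describes a regression for each variable and no joint model that would pull chance findings together.

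What is at stake is how the secondary results may be described. The planning values in Sample size {14} make this practical. At V1 they assume means of 2.10 (CFT) and 2.20 (ESS), SD 0.41 and 84 per group. The standard error is 0.41 × √(2/84) = 0.063, so z = 0.10/0.063 = 1.58, and unadjusted two-sided power is about 35%. Baseline adjustment with an assumed correlation of 0.7 raises it to about 60%. The CFT–ESS primary contrast could therefore miss even if the assumed effect is real, and readers would then turn to the secondary results.

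**Working it through.** The document gives no family-wise error figure for the secondary outcomes, so there is none to reproduce.

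**Inputs from the document.** Cut-offs of 0.975 and 0.025; 11 instruments, each at V1 and V2; three arms with equal allocation; 84 evaluable patients per group.

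**Assumptions, because the document does not state them.** Threshold value 0; two contrasts per outcome (CFT–ESS and CFT–TAU); equal SDs across arms; between-visit correlation 0.5 to 0.7; between-scale correlation 0 to 0.9; near-flat priors.

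**Step 1: error per test.** On the standardized scale the variance of a contrast is s² = 2/84 = 0.0238. With a normal prior centred on 0 with SD τ, the posterior probability passes 0.975 or 0.025 when |z| > 1.96/√f, where f = τ²/(τ² + s²).

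- τ = 0.5: f = 0.25/0.2738 = 0.913; critical |z| = 2.05; error 4.0%
- τ = 1: error 4.7%
- τ = 2.5: error 5.0%

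The rule therefore acts as a two-sided test at about 4 to 5%.

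**Step 2: number of tests and expected false effects.** 11 × 2 × 2 = 44 tests, and 44 × 0.05 = 2.2 false effects if all arms are equal. With τ = 0.5 this is 44 × 0.040 = 1.8. ISMI at V2 would add two tests (46; 46 × 0.05 = 2.3). Subscales, mediation and acceptability are not counted.

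**Step 3: chance of at least one false effect.** If all 44 tests were independent it would be 1 − 0.95^44 = 90%. They are not independent: both contrasts share the CFT arm, visits are correlated and scales are correlated. The table comes from a simulation of 11 equally correlated scales, two visits and three equal arms with no true effect. A test counts as a false effect when |z| > 1.96 (second column) or z > 1.96 in CFT's favour (third column). Ranges cover between-visit correlation 0.7 to 0.5.

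| Between-scale correlation | Either direction | Favouring CFT |
|---|---|---|
| 0 | 83–86% | 57–60% |
| 0.3 | 77–80% | 45–48% |
| 0.5 | 68–71% | 36–39% |
| 0.7 | 54–58% | 28–30% |
| 0.9 | 35–38% | 18–19% |

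The expected number stays at about 2.2 in every row. Higher correlation only gathers the false effects into fewer trials.

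**The case against.** **Multiplicity is usually left to the SAP.** A condensed article often omits the ordering and reporting language for secondary outcomes. That would settle the matter if the article were silent. It is not: it states a rule, under a heading that names both primary and secondary outcomes, for any effect. An SAP that treated secondary results differently would have to depart from this text.

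**A hierarchy already exists.** A reader might infer that the plan has none. The document does not support that: ISMI V0–V1 is the sole primary outcome and the rest are labelled secondary. What is missing is an order, or a supportive or exploratory label, within the secondary set.

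**The size depends on unstated inputs.** This stands. The threshold value, contrasts, prior scale and correlations are not given. A threshold requiring a worthwhile benefit rather than any benefit would lower the rate of false claims for CFT, and so would tighter priors; the more informative priors are planned only as a sensitivity analysis.

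**A favourable secondary finding is not expected by chance.** A reader might infer that it is, from the 2.2 expected false effects. But those count both directions. The chance of one favouring CFT passes one half only when the scales are nearly uncorrelated.

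**The Discussion does not offer a fallback.** A reader might see in "if our 12-session group program produces a significant decrease in self-stigma and shame scores" a claim resting on secondary results alone. The sentence also requires a fall in self-stigma and a long-term gain in social inclusion, and it says only that the program could then become an option. It is also discussion text, not a decision rule. It does show that shame and social inclusion are meant to carry weight in the interpretation.

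**Unadjusted secondary outcomes with 95% intervals are common practice.** Agreed. The difficulty is the word significant, not the intervals.

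**Conclusion.** The point holds in a limited form. As written, one unadjusted 0.975/0.025 rule covers every effect, and nothing tells the reader that secondary results are of a different kind. Given threshold 0, near-flat priors, two CFT contrasts and equal arms, at least one false secondary effect in some direction is more likely than not for between-scale correlations up to about 0.7, and falls to about 35–38% at 0.9. A false effect favouring CFT is less likely, at roughly 18–60% over the whole range.

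A reader might infer that the trial's main result is compromised. It is not: the primary ISMI comparison, the sample size and the data collection are unaffected. The change is worth making because it alters what the trial may claim from its secondary results, and because it has to be made before results are seen.

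**What to change.** In Statistical methods for primary and secondary outcomes {20a}:

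1. Limit the significance rule to the primary ISMI V0–V1 contrasts, CFT versus ESS and CFT versus TAU.
2. State that the secondary outcomes, all V2 results (including "To evaluate the maintenance of effects on self-stigma scores in the three groups of treatment (CFT, ESS, and TAU) at 6-month follow-up (V2")), the mediation analysis and the acceptability comparisons are supportive or exploratory. Report them as posterior estimates with the 95% credible intervals already planned, without the label significant.
3. If the sponsor wants a confirmatory claim on a secondary outcome, it should pre-specify its own short ordered list, tested only after the primary contrasts succeed. Which outcomes to list, and in what order, is the sponsor's choice.

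The cost is a few sentences, with no additional patients, data or modelling. The downside is that secondary results outside such a list cannot be claimed as confirmed effects.
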